## Abstract

**Background:**

The identification of the vitamin D receptor in the endocrine pancreas suggests a role for vitamin D in insulin secretion. There is also some limited evidence that vitamin D influences insulin resistance, and thus the early stages of the development of type 2 diabetes.

**Methods:**

Eighty-four women of South Asian origin, living in Auckland, New Zealand, were randomised to receive either a supplement (4000IU 25(OH)D_3 _per day) or a placebo for 6 months. At baseline, all participants were vitamin D deficient (serum 25(OH)D_3 _<50 nmol/L), insulin resistant (HOMA-IR > 1.93) and/or hyperinsulinaemic, hyperglycemic or had clinical signs of dislipidaemia. Changes in HOMA-IR, lipids, parathyroid hormone, calcium and bone markers were monitored at 3 months and 6 months.

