### Vitamin D intervention

Initial screening (phase 1 of the study) took place over a period of 9 months, commencing February 2007. See Table 1 for outcome measures and testing methods for phase 1. From the 250 women screened in phase 1, 116 qualified for phase 2, with the inclusion criteria described above. Women with FPG >7.2 mmol/L were offered a second blood test, and then withdrawn from the study and referred to their medical practitioner if the second blood test yielded similar results.

**Table 1 T1:** Outcome measures and testing methods used for phase one.

**Measure**	**Method**
**Blood analysis**	All analysed by LabPlus, Auckland City Hospital, Auckland
Fasting plasma insulin	Micro-particle enzyme immunoassay technology (MEIA), Abbott Diagnostics
Fasting plasma glucose	An enzymatic colourimetric assay; Roche Glucose reagent kit (Cat. No. 1876899)
Total cholesterol	Enzymatic colourimetric method (Roeschlau and Allain). Roche Cholesterol reagent kit (Cat. No. 1491458)
Triglycerides	Enzymatic conversion. Roche Triglycerides reagent kit (Cat. No. 1727711)
HDL-C	Homogenous enzymatic colourimetric assay. Roche HDL-Cholesterol Plus reagent kit (Cat. No. 04713214)
LDL-C	Calculated
Serum calcium	Colourimetric assay. Roche Calcium reagent kit (Cat. No. 1730240)
Serum albumin	Colourimetric assay. Roche Albumin Plus reagent kit (Cat. No. 1970909)
Serum high sensitivity CRP	Particle enhanced immunoturbidimetric assay. Roche CRPLX reagent kit (Cat. No. 03002039)
Serum parathyroid hormone	"ECLIA" electrochemiluminescence immunoassay. PTH Reagent Pack (Cat. No. 11972103122)
Serum 25 OH vitamin D	Radioimmunoassay, DiaSorin RIA kit (Cat. No. 68100E)

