**Questionnaires:**	
Dietary assessment	4-day food diary. Completed by subjects. Analysed using Foodworks 2007 (Xyris Software). Additional recipes and food lists provided by Indian dietitian
Medical and family history	Questionnaire administered following blood tests
Demographics	

One hundred and six women were recruited for phase 2, but a number were lost to the study due to becoming pregnant (n = 3), moving overseas (n = 6) perceived side-effects (n = 2), medical practitioner prescribing vitamin D (n = 3), or withdrew from study (n = 8).

The intervention consisted of a 25(OH)D_3 _supplement, 4000 international units (IU) per day, or placebo, in the form of 4 oral capsules, for 6 months. The consumption of 4000 IU 25(OH)D_3 _has been shown to be a safe and effective dose [32,33]. The active supplement was tested for 25(OH)D_3 _content by the Massey University Nutrition laboratory. The average content per dose was 4226 IU, no vitamin D was detected in the placebo. The vitamin D content will be tested again at the completion of the study to determine any degradation during storage over the period of the study.

Subjects were matched into pairs by age and BMI. Randomisation of the active/placebo capsules and allocation to pairs was performed by Blackmores using nQuery Advisor^®^, version 6.0, (Statistical Solutions, Cork, Ireland). Randomisation and allocation were fully concealed from the researchers.

Once recruited into phase two, participants were recalled for a baseline blood test prior to being given their supply of supplements. After 3 months another blood sample was taken to check for hypercalcaemia. Once the intervention was completed (6 months) participants provided one more blood sample and were weighed again. See Table 2 for outcome measures and testing methods for the intervention phase of the study.

**Table 2 T2:** Outcome measures and testing method for phase two (measured at baseline, 3 months and 6 months)

**Test**	**Method**
Blood tests As listed in table 1, plus:	
Collagen C-telopeptide (CTX) Osteocalcin (OC)	Roche Elecsys beta cross-laps Roche Elecsys 2010 Canterbury District Health Board Laboratory
Weight at baseline and 6 months	Tanita electronic scales

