### Data Handling and statistical analysis

Name and address details were maintained in Microsoft Access. Check boxes recorded the progress of a participant through the study and thus allowed personalised letters to be sent to groups of participants as required throughout the study. All other data were entered into a single Microsoft Excel spreadsheet with participants identified only by their unique Subject Number. All entries were double-checked by another member of the research team.

Before commencement of statistical analysis the data will be cleaned and checked for coding errors. Descriptive statistics will be used for the baseline population characteristics: mean (SD), median, mode and range summary statistics, independent t-tests and paired t-tests for numerical normally distributed data, and Mann Whitney U and Wilcoxon Paired Rank Test (for paranormal distribution) and Chi-Squared tests (for categorical data). Spearman (checked with Pearson) correlations and ANOVA will be calculated to test for associations between variables.

The primary analysis will be a comparison of the change of the primary outcome (vitamin D status) between the intervention and the control group following the 'intention to treat' principle at three months and six months. In order to assess whether protocol deviations have caused bias, the results of the intention-to-treat analyses will be compared to 'per protocol' analyses. Furthermore secondary analyses will be performed to explore intervention effects on the insulin resistance, HDL/triglycerides and bone markers. Analysis of covariance will be used to analyse the effects of treatment on changes in variables while controlling for the effects of possible confounding factors for example different baseline conditions (e.g. BMI). Statistical analyses will be performed by using SPSS software (version 15).

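### The 84 women the abstract calls randomised appear to be those remaining after 22 losses from 106, so the number randomised and the intention-to-treat set need correcting

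*Protocol article*

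**What the plan says.** Three parts of the protocol article bear on this point.

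- **Abstract, Methods.** "Eighty-four women of South Asian origin, living in Auckland, New Zealand, were randomised to receive either a supplement" or placebo for 6 months. No other number in the article is described as randomised.
- **Vitamin D intervention section.** Eligibility is given first: "From the 250 women screened in phase 1, 116 qualified for phase 2". The text after Table 1 continues: "One hundred and six women were recruited for phase 2, but a number were lost to the study". The reasons listed are "becoming pregnant (n = 3), moving overseas (n = 6) perceived side-effects (n = 2") and "medical practitioner prescribing vitamin D (n = 3), or withdrew from study (n = 8"). The same section says that women, once recruited, came back for a baseline blood test before they were handed their supplements.
- **Data Handling and statistical analysis.** The primary analysis compares the change in vitamin D status between arms at 3 and 6 months on the intention-to-treat principle. To see whether protocol deviations have caused bias, "the results of the intention-to-treat analyses will be compared to" per-protocol results. No denominator is given for either set.

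**The concern.** A count labelled as randomised should be the number allocated, before any attrition. Here it equals, to the woman, the number left after a list of losses that includes at least one reason arising only after treatment has started.

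Intention to treat means analysing everyone randomised in the arm to which she was randomised. If the abstract's 84 is taken at its word as the randomised set, allocated women drop out of the primary analysis before it begins.

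Two of the listed reasons matter most. Women who stopped for perceived side-effects left for a reason tied to treatment. Women prescribed vitamin D by a practitioner, if this happened after allocation, are protocol deviators whom intention to treat keeps. The analysis section names vitamin D status as the primary outcome, so removing those women selects on a direct cause of that outcome. Removing such women from the placebo arm would tend to widen the apparent difference between arms.

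The comparison with per protocol would also lose force, because some of the deviators it is meant to expose would already be missing from both sets.

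**Working it through.** **Inputs.** Recruited to phase 2: 106. Losses: pregnancy 3, moving overseas 6, perceived side-effects 2, vitamin D prescribed 3, withdrew 8 (all from the Vitamin D intervention section). Stated as randomised: 84 (Abstract). Required sample: 42 per arm (Participants section).

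**Step 1: reproduce the 84.**
- Losses: 3 + 6 + 2 + 3 + 8 = 22.
- Remaining: 106 - 22 = 84, exactly the abstract's figure.
- It also equals the sample size target, 2 x 42 = 84.

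**Step 2: can both statements be true?** Only if all 22 losses came before allocation. Capsules were handed out after recruitment and after the baseline blood test. A woman who left because of perceived side-effects must have been given capsules, and so must already have been allocated. Both statements therefore cannot stand as written.

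**Step 3: range for the number randomised.**
- Lower end, only the 2 side-effect losses after allocation: 84 + 2 = 86.
- Upper end, all 22 losses after allocation: 84 + 22 = 106.
- The other 20 losses (3 + 6 + 3 + 8) are not dated, so the article does not fix a value within this range.

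**Step 4: share of allocated women omitted if the 84 were analysed.**
- Lower end: 2/86 = 2.3%.
- Upper end: 22/106 = 20.8%.

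**Step 5: what omission could do (illustration on assumed values).** If a fraction p of an arm is omitted, and their mean change differs from that of the remaining women by d, the arm mean is off by p x d. Assume equal losses per arm, d = 0.5 HOMA-IR units, and opposite directions in the two arms. None of these assumptions comes from the article.
- All 22 after allocation, 11 of 53 per arm: 2 x 0.5 x 11/53 = 0.21, or 21% of the 0.98 reduction used for the power calculation.
- Only the 2 after allocation, 1 of 43 per arm: 2 x 0.5 x 1/43 = 0.023, or about 2% of 0.98.
- If p and d are the same, with the same sign, in both arms, the errors cancel and the difference between arms is unaffected.

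**The case against.** The strongest reply is that the article commits to intention to treat and never says the set is the 84. It says women were lost to the study, not that they are left out of the analysis, and an article may leave the exact definition of the set to a fuller document. That stands: a reader might infer that the planned analysis is a completers analysis under another name, but the document does not say so. What survives is that a stated count conflicts with other stated counts, and the only figure attached to randomisation is the one in doubt.

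The word completers is also unsupported. The abstract and the intervention section describe follow-up in the past tense, but retesting of the capsules and feedback to participants at the end of the trial are still in the future. The 84 are the women remaining after the listed losses; none is shown to have finished 6 months.

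The timing objection is fair as well. The 106 are described as recruited, not randomised, and there was an interval between recruitment and capsule supply. Pregnancies, moves overseas, prescriptions and withdrawals could have fallen in it. However, the article does not say whether allocation took place at capsule supply or earlier, so leaving in that interval does not prove that a woman was unallocated.

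Nor should all 22 losses be called treatment-related. Side-effects, prescribed vitamin D and withdrawal come to 2 + 3 + 8 = 13 (12.3% of 106), and the 8 withdrawals have no stated reason.

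Finally, the per-protocol comparison would be weakened but not emptied: a per-protocol set could still drop poor adherers among the 84.

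**Conclusion.** The point holds as an error in the count with a conditional consequence for the analysis. The abstract's 84 appears to be the number remaining after losses, and the number randomised is probably between 86 and 106. The lower end rests on reading perceived side-effects as effects of the study capsules, which is the natural reading.

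If the intention-to-treat analysis is run on the 84, it omits 2 to 22 allocated women (2.3% to 20.8%) and is not intention to treat. A reader might take one-fifth exclusion, or a bias of 21% of the planned effect, as established. Neither is. The first requires every loss to follow allocation. The second also requires an assumed difference of 0.5 in opposite directions in the two arms, and it concerns HOMA-IR, which the analysis section treats as secondary.

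The correction should still be made before analysis, because the randomised count determines who belongs in the primary comparison.

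**What to change.** 1. Correct the abstract to the number of women actually allocated, and give it by arm.
2. Report the 22 losses by arm, reason and timing relative to allocation. Describe the 84 as the women remaining after losses.
3. Define the intention-to-treat set as every allocated woman in her allocated arm, including any who stopped for perceived side-effects or were prescribed vitamin D after allocation. Use all available baseline, 3-month and 6-month data.
4. Define the per-protocol set as a subset of that set, so that the planned comparison can show the effect of deviations.
5. Optionally, add a sensitivity analysis for missing outcomes.

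The analysis is still to come, so the cost is small: a check of the allocation records, a corrected count and a few sentences of analysis wording. Some lost women will have only baseline or 3-month data, so intervals may be slightly wider, and the reported attrition will look less favourable than it does now.

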**Discussion:**

This randomised, controlled trial will be the first to investigate the effect of vitamin D supplementation on insulin resistance in non-diabetic subjects. It will subsequently contribute to the growing body of evidence about the role of vitamin D in metabolic syndrome.Registered clinical.

**Trial registration:**

Registered clinical trial – Registration No. ACTRN12607000642482

## Background

Hypovitaminosis D is becoming recognised as a worldwide problem, and exists even in countries such as New Zealand and Australia which enjoy plentiful sunshine and latitudes sufficiently moderate to allow some endogenous synthesis throughout the year [1-5]. Once thought to impact only on bone health, there is now evidence to implicate vitamin D deficiency in a plethora of adverse health conditions such as cancer and auto-immune diseases. There is mounting interest in the role of vitamin D in the constellation of metabolic abnormalities grouped under the term "metabolic syndrome", including hypertension, dyslipidaemia, abdominal obesity, glucose intolerance and type 2 diabetes.

Low serum vitamin D has been shown to correlate with impaired glucose tolerance [1,6-8], whilst administration of supplemental vitamin D to subjects with elevated blood glucose levels has resulted in an improvement in insulin secretion [9,10]. Similar improvements have been observed in vitamin D-deficient subjects following supplementation [6,11].

The role, if any, that vitamin D deficiency plays in insulin resistance has had little investigation. Whilst a correlation between hypovitaminosis D and insulin resistance has been identified in pregnant women [12] and obese adolescents [13] randomised, controlled trials with vitamin D supplementation are sparse, especially in non-diabetic, insulin resistant, vitamin D deficient subjects. Borissova et al [10] measured a 29% (but not significant) decrease in HOMA-IR following supplementation of 1332IU 25(OH)D_3_/day for one month in a group of 10 diabetic women, 70% of whom were vitamin D deficient (<50 nmol/L). Pittas et.al. [14] saw a significantly lower increase in HOMA-IR in vitamin D/calcium supplemented subjects with impaired fasting glucose, compared to those receiving calcium only, but subjects were not vitamin D deficient. Meanwhile, Taylor [15] reported an increase in insulin resistance in 3 diabetic patients following a single intramuscular dose of 300,000 IU of 25(OH)D_2_.

The importance of vitamin D in the maintenance of the calcium economy and bone health is well known. A significant positive correlation has been found between serum vitamin D levels and bone mineral density in South Asians living in India [16], Britain [17] and Bangladesh [18]. An inverse relationship has been identified between vitamin D status and OC, a marker of bone turnover [19]. Bone markers are useful for identifying changes in bone metabolism, particularly when monitoring intervention or therapy [20].

The population of interest in this study is women of South Asian origin living in Auckland, New Zealand. There is a high incidence of type 2 diabetes in South Asians living in New Zealand; self-reported diabetes is over three times higher for this group compared to national incidence [21]. The possibility of an ethnic or genetic predisposition to develop diabetes in this population is supported by epidemiological evidence from around the world [22] and India itself where there are over 33 million people diagnosed with diabetes [23].

Between 1991 and 2001 the numbers of Asian Indians living in New Zealand doubled. This trend has continued exponentially with a current population of over 113,000 South Asians living predominantly in the Auckland area [24]. The projections for future growth indicate that the Asian population of which Indians are the second largest group will increase from 272,000 in 2001 to 667,000 by 2021, an increase of 395,000 (145%) [24].

Very little is known about vitamin D status of this population. However, a number of studies suggest that South Asian migrants may have a higher risk of disease states associated with low vitamin D status such as infantile rickets, osteoporosis and both type-1 and type-2 diabetes [22,25,26]. Reasons for low vitamin D status are various and mostly unconfirmed. They include low incidental exposure to sunlight, deliberate avoidance of sunlight, limited dietary intake of vitamin D (there is no routine fortification of the New Zealand food supply with vitamin D) and possibly genetic factors. Polymorphisms in the vitamin D receptor, which are thought to modify susceptibility to diabetes, have been identified in both Indian and Bangladeshi populations [27].

### Hypotheses

• There is a high prevalence of hypovitaminosis D in South Asian women living in Auckland, New Zealand.

• Supplementation of vitamin D in subjects who have demonstrated insulin resistance and vitamin D deficiency will result in an improvement in markers for metabolic syndrome.

• Supplementation of vitamin D in subjects who have demonstrated vitamin D deficiency will result in an improvement in bone marker ratios in favour of bone mineralisation.

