### Aims

• To establish the vitamin D status of South Asian women living in Auckland, NZ.

• To investigate the effectiveness of vitamin D supplementation in improving insulin sensitivity in women with hypovitaminosis D who have demonstrated insulin resistance, and/or lipid profiles in those with dyslipidaemia.

• To investigate the effect of vitamin D supplementation on bone marker ratios in women who have hypovitaminosis D.

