### Participants

It was calculated that 42 subjects would be required for each arm of the trial to demonstrate a significant difference at 80% power and 5% significance. Power calculations were based on the results of a lifestyle intervention which achieved a reduction in HOMA-IR of 0.98 [28], and derived from Margetts and Nelson [29].

Women were invited to participate in the study through advertisements in suburban and Auckland newspapers, and Indian media such as television, radio and newspapers. Posters and leaflets were distributed in a number of venues around Auckland such as General Medical Practices with high numbers of South Asian patients, clubs, and temples. A number of South Asian social and community groups were given presentations about the study by the researchers.

A short television documentary on a channel popular with Indian viewers elicited the greatest response of all the methods used. However, the most effective form of promotion was word-of-mouth. A relatively small group of supportive women from the South Asian community promoted the study and were instrumental in the successful recruitment of 250 women.

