## Discussion

The information that was obtained from the screening phase of this study provided a valuable and unique insight into this rapidly increasing group of migrants entering New Zealand. It was not the intention during this phase to conduct a cross-sectional study and there was no attempt to recruit in a fully randomised way. Indeed, such recruitment in any specific, ethnic minority within a large population would be highly problematic. However, the 250 women who participated in phase one of the Surya Study represent approximately 0.5% of the total number of South Asian women living in New Zealand. Distribution in terms of country of origin reflected that of the entire population as reported in the 2006 census [24]. Level of education, although higher than the New Zealand national average, was as expected of a newly migrant population given New Zealand's immigration requirements for high educational standards [37].

As far as we are aware, there has been no other randomised, placebo-controlled, double-blind trial investigating the effect of vitamin D supplementation on insulin resistance and other markers of metabolic syndrome. If this trial is successful, it will provide another clue about the aetiology of type 2 diabetes, and the opportunity to reduce one of the many risk factors.

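### No test is named as deciding hypothesis 2: the trial is sized on HOMA-IR, but the analysis section lists insulin resistance unranked beside lipids as exploratory

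*Protocol article*

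**What the plan says.** Five places in the protocol article bear on this point.

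- **Hypotheses.** The second hypothesis is directional and its outcome is a plural, open set: supplementation "will result in an improvement in markers for metabolic syndrome".
- **Aims.** The matching aim is to investigate insulin sensitivity in women "who have demonstrated insulin resistance, and/or lipid profiles in those with dyslipidaemia".
- **Participants.** The calculation gives 42 women per arm to "demonstrate a significant difference at 80% power and 5% significance". It is based on a HOMA-IR reduction of 0.98 seen in a lifestyle intervention.
- **Data Handling and statistical analysis.** The primary analysis is a "comparison of the change of the primary outcome (vitamin D status) between the intervention and the control group". The metabolic outcomes follow: "Furthermore secondary analyses will be performed to explore intervention effects on the insulin resistance, HDL/triglycerides and bone markers". No order is given among them.
- **Abstract (Methods) and Table 2.** "Changes in HOMA-IR, lipids, parathyroid hormone, calcium and bone markers were monitored" at 3 and 6 months. Table 2 carries forward the blood tests of Table 1, which include fasting insulin, glucose, triglycerides, HDL-C, LDL-C and total cholesterol.

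The Discussion adds: "If this trial is successful, it will provide another clue about the aetiology of type 2 diabetes".

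**The concern.** These sections do not agree on what decides hypothesis 2. The sample size treats HOMA-IR as the outcome to be demonstrated. The hypothesis refers to metabolic markers in general. The aim allows insulin sensitivity, lipids or both. The analysis section calls all of them exploratory and ranks none.

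Suppose triglycerides improve at a nominal 5% level and HOMA-IR does not. The hypothesis and aim allow this to be reported as support. On the comparison behind the sample size, the trial would have shown nothing. The document gives no rule for choosing between these readings, so the choice could be made after the results are known. A claim that can be reached by more than one route also carries a higher false-positive rate than the 5% on which the trial was sized.

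The point concerns several markers at one visit. Using both the 3- and 6-month visits would add to it, but that is a separate matter.

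**Working it through.** **Step 1: the plan's own figure.** For two means, n per arm = 2(z₀.₉₇₅ + z₀.₈₀)² × (SD/Δ)², with Δ = 0.98. The article gives no SD and no sidedness, so 42 can be neither confirmed nor refuted. Solving back, two-sided, SD = 0.98 / [(1.960 + 0.842) × √(2/42)] = 1.60; the one-sided equivalent is 1.81. An SD of 1.6 gives 2 × 7.849 × (1.6/0.98)² = 41.8, that is 42. The 5% therefore belongs to a single HOMA-IR comparison. The missing SD does not affect what follows.

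**Step 2: number of markers, k.**
- The analysis section names two metabolic outcomes, insulin resistance and HDL/triglycerides, so k = 2. Bone markers belong to hypothesis 3.
- If HDL and triglycerides were tested separately, k = 3.
- A broad reading gives k = 6: fasting insulin, glucose, triglycerides and HDL-C (Table 1), HOMA-IR (Abstract, Participants) and the triglyceride/HDL ratio (inclusion criteria). The article does not say that all six will be tested.

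**Step 3: error rates.** Assumptions: no true effect on any marker, one visit, each test two-sided at 5%, any one marker counted as confirmation, and a common correlation ρ between the test statistics.
- Independent markers: P(false improvement) = 1 − 0.975ᵏ; P(any significant result) = 1 − 0.95ᵏ. For k = 2: 1 − 0.975² = 4.9% and 1 − 0.95² = 9.75%.
- Correlated markers: P(false improvement) = 1 − ∫ φ(u) Φ[(1.96 − √ρ u)/√(1 − ρ)]ᵏ du. The either-direction rate uses the two-sided acceptance region in place of Φ.

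| k | ρ | False improvement (nominal 2.5%) | Either direction (nominal 5%) |
|---|---|---|---|
| 2 | 0 | 4.9% | 9.75% |
| 2 | 0.5 | 4.5% | 9.1% |
| 2 | 0.8 | 3.9% | 7.8% |
| 3 | 0.5 | 6.3% | 12.5% |
| 6 | 0.5 | 10.4% | 20.7% |
| 6 | 0.8 | 6.9% | 13.9% |
| 6 | 0 | 14.1% | 26.5% |

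**Step 4: can six markers be independent?** No. HOMA-IR is computed from insulin and glucose, and the ratio from triglycerides and HDL-C, so the last row cannot occur. A simulation on the log scale built the two derived markers from four base markers, with three sets of assumed base-marker SDs. With independent base markers it gave 10.6% to 11.3% false improvement and 20.5% to 21.7% in either direction. With base-marker correlations of 0.3 it gave 9.3% to 9.6% and 18.5% to 19.0%.

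**Step 5: if one test decides.** The rates return to 2.5% for a false improvement and 5% in either direction.

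**The case against.** The strongest reply is that the article already limits these analyses: they are secondary, meant to explore, and sit beside a single primary outcome. Alpha sharing among secondary outcomes is normally left to an analysis plan, and none is shown here. That reply holds against any complaint that a multiplicity procedure is missing. It does not remove the conflict in the stated text. The same outcome supplies a directional hypothesis and the basis of the sample size, and is then called exploratory. An analysis plan would inherit that conflict.

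A second reply is that the aim's and/or pairs each outcome with its own women, insulin sensitivity with the insulin resistant and lipids with the dyslipidaemic, mirroring the alternative entry criteria. This is a fair reading. It still leaves two routes under one hypothesis.

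A reader might infer three stronger things that the document does not support.

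- **That a false improvement has a 9% to 27% chance.** Those are either-direction rates, which also count false worsening, and the top needs six independent markers.
- **That one significant marker confirms the hypothesis under the plan as written.** No section states such a rule; it is one reading the wording permits. Nor is 5% per marker stated: the 5% appears only with the sample size.
- **That a significant lipid result with a non-significant HOMA-IR gives opposite conclusions.** A non-significant HOMA-IR result is absence of proof, not proof of no effect.

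The Discussion's reference to success is weak support, since the same sentence promises only a clue.

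**Conclusion.** The point stands in a limited form. The hypothesis, the aim, the sample size and the analysis section do not agree on which result decides hypothesis 2, and HOMA-IR, on which the trial was sized, is given no deciding role.

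On the two metabolic outcomes the analysis section names, the false-improvement rate is about 1.6 to 2 times nominal. On the broad six-marker reading it is roughly 3 to 4.5 times nominal. Both multiples depend on the assumed marker count, test level, correlations and any-one-marker rule. The inconsistency between sections depends on none of them and is the firmer part of the finding. It is worth correcting because the correction is cheap; the error rates alone would not make it a grave fault.

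**What to change.** In Data Handling and statistical analysis, name the between-group difference in HOMA-IR at 6 months as the single test that decides hypothesis 2, two-sided at 5%, consistent with the sample-size section. State that the lipid, insulin and glucose results are supportive, are reported with estimates and 95% intervals, and do not by themselves confirm the hypothesis.

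Decide this together with the mismatch between a sample size built on HOMA-IR and a primary outcome of vitamin D status, since one revision can resolve both.

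The cost is one or two sentences, written before unblinding, with no new data or participants. The downside is that an isolated lipid or glucose result can no longer be claimed as confirming hypothesis 2. Going further, by removing lipids from the hypothesis or testing them only after a significant HOMA-IR result, is a debatable trade-off and is not needed here: women could enter the trial on the triglyceride/HDL ratio alone, and lipids are part of the stated aim.
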